**Enrollment**											
	Eligibility screen	✓									
	Informed consent	✓									
	Allocation										
**Interventions**											
	Aerobic training			✓		✓					
	Behavior intervention			✓		✓					
**Assessments**											
	Lung function					✓					
	PADL^a^ and sedentary behavior	✓						✓		✓	
	Asthma clinical control	✓						✓		✓	
	Asthma exacerbation					✓		✓		✓	
	Quality of life					✓		✓		✓	
	Anxiety and depression symptoms					✓		✓		✓	
	Barriers to performing PADL					✓		✓		✓	
	Behavioral stage for PADL					✓		✓		✓	
	Anthropometric data					✓		✓		✓	
	Body composition					✓		✓		✓	
	Sleep quality					✓		✓		✓	
	CPET^b^					✓		✓		✓	

^a^PADL: physical activity in daily life.

^b^CPET: cardiopulmonary exercise testing.

### Outcome Measures

The primary outcome will be to compare the effects of AT and BI to increase the PADL on clinical asthma control. The secondary outcomes will include quality of life, sleep quality, asthma exacerbations, anxiety and depression levels, barriers that hinder the practice of PADL, body composition, and anthropometric data.

#### Primary Outcome: Asthma Clinical Control

Clinical asthma control will be assessed using the ACQ, a reliable and validated tool [18,33] that comprises 7 questions [18]. Of those, 5 questions are related to asthma symptoms (waking up at night, activity limitations, shortness of breath, and wheezing), one on rescue medication (short-acting β_2_-agonist use), and one on lung function (FEV_1_ prebronchodilator, expressed as a percentage of predicted value). The questions are indicated on a 7-point scale ranging from 0 (no limitation) to 6 (maximum limitation), and the total score is the average of the 7 items, ranging from 0 (fully controlled) to 6 (severely uncontrolled). It is considered that values ≥1.5 indicate poorly controlled asthma, 0.75 to 1.5 indicate partially controlled asthma, and ≤0.75 indicate fully controlled asthma [18]. A change of at least 0.5 points in the ACQ score is considered clinically significant [34].

#### Secondary Outcomes

#### Physical Activity in Daily Life

PADL will be objectively assessed using an activity monitor (ActiGraph GT9X, ActiGraph), a device that monitors frequency, intensity, and duration [35] in real time and is a sensitive and reliable method [36,37]. This triaxial monitor provides measurements for the amount and intensity of PADL and posture monitoring [35,38] through variations in acceleration. The “counts” obtained during a given period are linearly related to the intensity of the patient’s physical activity in that period [37]. Patients will be instructed to use the accelerometer for 7 consecutive days on the hip secured with an elastic belt. All accelerometers will be initialized to collect data in 60-second “epochs” in the 3 axes via ActiLife software (version 6.9.5; ActiGraph). The data will be analyzed using the same software, including the number of daily steps; the time spent engaging in sedentary behavior; and light, moderate, and vigorous activities. Moderate to vigorous physical activity will also be assessed.

#### Asthma-Related Quality of Life

Health-related quality of life will be evaluated using the Asthma Quality of Life Questionnaire [39,40]. This questionnaire consists of 32 questions related to the previous 2 weeks and is divided into 4 domains: activity limitation (11 items), symptoms (12 items), emotional function (5 items), and environmental stimulus (4 items). The Asthma Quality of Life Questionnaire score ranges from 0 to 7; a higher score will be associated with better quality of life. A difference of 0.5 points is considered clinically significant [41].

#### Sleep Quality

Sleep quality will be assessed via a monitor (ActiGraph GT9X, ActiGraph) worn on the participant’s nondominant wrist. The participants will be instructed to wear the device for 7 consecutive nights. The results for sleep latency (the amount of time required to fall asleep) and sleep efficiency (the number of sleep minutes divided by the total number of minutes the participant was in bed) will be analyzed [8]. The device is valid and reliable for detecting sleep/wake diurnal patterns [42]. In addition, participants will receive a diary for routine analyses covering these 7 nights (time participants went to sleep, time they woke up, and went to sleep on a scale of 0-10).

#### Asthma Exacerbation

Asthma exacerbation is defined as the patients’ need for urgent medical action and a change in pharmacological treatment [43]. During the study, at least one of the following criteria will be used to determine an exacerbation: the use of ≥4 puffs of rescue medication per 24 hours during a 48-hour period; the need for the administration of systemic corticosteroids (pills or injections); or unscheduled medical appointments, visits to the emergency room, or hospitalization [26,32,43].

#### The Behavioral Stages for Physical Activity

The “readiness for change” assessment will be graded through a questionnaire to assess the following behavioral stages for physical activity: *precontemplation*, *contemplation*, *preparation*, *action*, and *maintenance* [31,44]. Information will be revealed as frequency.

#### Barriers to Performing Physical Activity

Barriers to the practice of PADL will be assessed via a questionnaire that contains the most common barriers in adults [45,46]. The answer options for each question will include never, rarely, sometimes, almost always, and always, with the score for each item ranging from 0 to 4. Higher scores indicate greater barriers. At the end of the questionnaire, a question regarding the limitations of PADL resulting from the disease will be added, which will receive the same score as the previous questions.

#### Body Composition and Anthropometric Indexes

Octopolar InBody 720 equipment (Biospace) will be used to measure body weight, fat mass, fat-free mass, visceral adiposity area, and skeletal muscle mass. The InBody 720 uses 8 electrodes to assess body composition according to total body water, protein, mineral, and fat mass. The contact points for the electrode connection will be cleaned with an electrolytic cloth, according to the manufacturer’s instructions. At the time of testing, the patient should not be menstruating and will also be instructed not to ingest water for 4 hours and caffeine or alcohol for 12 hours before the test, or to perform physical activity or take a sauna the day before the test, and not to urinate 30 minutes before the test. The data will be electronically imported into Excel via LookingBody 3.0 software (Biospace). Anthropometric data, including height, body weight, abdominal circumference, waist and hip circumference, and waist-to-hip ratio, will be measured according to standardized protocols [47,48]. BMI will be calculated by dividing body weight (in kg) by height (in m^2^) [49].

#### Anxiety and Depression

The Brazilian Portuguese version of the Hospital Anxiety and Depression Scale will be used to assess the symptoms of anxiety and depression [50]. The Hospital Anxiety and Depression Scale consists of 14 questions divided into 2 subscales: anxiety and depression (7 questions each). Each question ranges from 0 to 3 points, with a maximum score of 21 points for each subscale. In this study, a cutoff score (≥9) will be used to classify the presence or absence of anxiety or depression [51].

#### Cardiopulmonary Exercise Testing

CPET will be performed via an electrical cycle ergometer (Corival; Lode BV Medical Technology) equipped with an electronic system (CPX System; CareFusion) [52]. Peripheral oxygen saturation (SpO_2_) and electrocardiography will be continuously monitored during the tests. The following variables will be recorded: work rate, oxygen consumption (VO_2_), minute ventilation, carbon dioxide production (VCO_2_), respiratory exchange rate, and HR [9]. Blood pressure, leg discomfort, and dyspnea will also be monitored using the Borg scale [53]. The participants will perform the CPET, which is limited by symptoms, consisting of 2 minutes of rest, 2 minutes of warm-up (unloaded pedaling), and a period of work on a ramp (from 5 to 15 W), with increments every minute, according to the participants’ daily activity level [9]. AT will be identified as the VO_2_ at which the change in the slope of the VCO_2_-to-CO_2_ ratio occurs. The RCP will be determined by the increased ventilation/VCO_2_ values, accentuated tachypnea, and a progressive reduction in end‐tidal CO_2_ pressure [9]. A 10% correction will be made in the HR at anaerobic threshold and RCP [54,55] because the test will be carried out on a bicycle, and training on a treadmill.

The test interruption criteria will include diastolic blood pressure above 140 mm Hg, sustained drop in systolic blood pressure, systolic blood pressure above 240 mm Hg, motor incoordination, feelings of imbalance, mental confusion, and clinical manifestations of respiratory distress exacerbated by increased workload or associated with electrocardiographic changes in ischemia and severe manifestations of exercise-induced bronchospasm, such as an excessive increase in ventilatory effort, audible wheezing, and signs of respiratory distress [56]. Patients will be instructed to use 400 μg of salbutamol via aerosols if necessary (peak flow, 70% predicted) [6,19,57].

### Statistical Analysis Planning

The sample size calculation (n) was established based on the clinical control measured by the ACQ to detect a clinical improvement of 0.5±0.6 points [34]. The required sample size will be 24 patients per group for a total of 48 patients, and a 15% loss will be considered, resulting in a total of 56 patients. The sample power was considered 80% with a significance level of 5%. Before the interventions, clinical, anthropometric, physical fitness, PADL, and psychosocial data obtained at baseline will be compared using the 2-tailed *t* test or Mann-Whitney test (depending on data normality) for continuous variables. The chi-square test will be used to compare categorical variables. After the intervention, time and group interactions will be evaluated using a two-way repeated measures ANOVA. The significance level will be adjusted at *P*<.05 for all tests, and the SigmaStat (version 3.5; Systat Software) program will be used for statistical analysis. All the analyses will follow the intention-to-treat principles until 15% of the data are missing. For confidentiality, the participants will be given an anonymous study ID, and only the study investigators will have access to the final trial dataset.

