## Methods

### Study Design

This study is a randomized trial with 2 parallel arms and a blinded evaluation. The study will be conducted at a university hospital that offers specialized treatment for moderate to severe asthma. The study protocol was developed in accordance with the SPIRIT (Standard Protocol Items: Recommendations for Interventional Trials) checklist guidelines [15], and the trial is registered at ClinicalTrials.gov (NCT05364632). The study flow diagram is presented in Figure 1.

After a regular medical visit, adult outpatients with asthma will be invited to participate in the study, and asthma pharmacotherapy will be maintained during the intervention. Initially, eligible patients will be randomized by a researcher not involved in the study using a computer-generated sequence into 2 groups: the AT group or the BI group. The total duration of each intervention for both groups will be 12 hours (720 minutes). Both groups will be evaluated before and after the interventions and again 16 weeks later. The evaluations will be carried out in a blinded fashion by an evaluator who will not be directly involved in the interventions.

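### The 80% power belongs to a single AT-BI difference in ACQ, but the planned test is a group-by-time ANOVA over three visits, with no primary contrast and no baseline covariate

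*Protocol article*

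**What the plan says.** The section Statistical Analysis Planning bases the sample size on ACQ, "to detect a clinical improvement of 0.5±0.6 points", with 80% power at the 5% level. It concludes: "The required sample size will be 24 patients per group for a total of 48 patients". Allowing for loss, "a 15% loss will be considered, resulting in a total of 56 patients".

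For the analysis, the same section states: "After the intervention, time and group interactions will be evaluated using a two-way repeated measures ANOVA". The Abstract names the same method. No covariate is mentioned. Baseline values enter only through between-group baseline tests and, by implication, as the first level of the time factor.

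On visits, Study Design says: "Both groups will be evaluated before and after the interventions and again 16 weeks later". The Abstract and Table 2 also show three ACQ assessments.

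On the primary outcome, the article says "Clinical asthma control will be assessed using the ACQ". Neither Outcome Measures nor Statistical Analysis Planning says which visit, or which comparison between the arms, is primary.

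**The concern.** The sample size and the test answer different questions. The calculation is for one contrast between two groups. An interaction over three visits asks whether the two mean profiles differ in shape in any way, and its power depends on how the group difference behaves at follow-up, which the plan does not specify.

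This matters for interpretation as well as power. The Objectives expect similar benefit from the two interventions, and Strengths and Limitations says it is essential to learn whether gains last. A significant interaction does not by itself show which arm is better, by how much or at which visit. A non-significant one is not evidence of similarity. Both questions need an estimate of AT minus BI at a named visit, read against the 0.5-point change that the article calls clinically significant.

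The model also uses baseline ACQ less efficiently than it could. Every patient has a baseline value, because ACQ of at least 1.5 is an entry criterion.

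**Working it through.** **Inputs from the article.** Difference 0.5; SD 0.6 (not said to be of change or of a single-visit score); power 80%; alpha 5%; 24 per arm, or 56/2 = 28 per arm with the loss allowance; three visits.

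**Assumptions.** Two-sided testing, because sidedness is stated only for the baseline comparisons ("compared using the 2-tailed" *t* test). Compound symmetry with within-patient correlation rho, which the article does not give; range 0.3 to 0.8.

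**1. Reproducing the stated size.** Normal approximation: n = 2 × 0.6² × (1.96 + 0.84)² / 0.5² = 22.6, so 23 per arm. The exact two-sample t-test gives 23.6, so 24 per arm, with 80.7% power at 24. The stated figure is therefore that of one two-group contrast.

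**2. Power of the planned interaction, 0.6 as SD of change.** The within-patient error variance is 0.6²/2 = 0.18. With d_j the AT-BI difference at visit j, noncentrality is lambda = (n/2) × Σ(d_j − mean d)² / 0.18, referred to F with 2 and 92 df at n = 24 (2 and 108 df at n = 28).

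| Difference at baseline, end of intervention, follow-up | Σ(d_j − mean d)² | lambda, n = 24 | Power, n = 24 | Power, n = 28 |
|---|---|---|---|---|
| 0, 0.5, 0.5 (fully kept) | 0.1667 | 11.1 | 84.4% | 89.9% |
| 0, 0.5, 0 (fully lost) | 0.1667 | 11.1 | 84.4% | 89.9% |
| 0, 0.5, 0.25 (half kept) | 0.1250 | 8.33 | 72.1% | 79.2% |

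The first two rows are identical: the omnibus test has the same power for a lasting difference and for one that has vanished, and significance alone does not tell them apart.

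**3. The same test, 0.6 as single-visit SD.** The error variance becomes 0.36 × (1 − rho). At n = 24:

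| rho | Fully kept | Half kept |
|---|---|---|
| 0.3 | 69.9% | 56.6% |
| 0.5 | 84.4% | 72.1% |
| 0.7 | 97.4% | 91.7% |

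**4. Baseline as covariate, one post-baseline visit.** With single-visit SD σ, the change score has variance 2σ²(1 − rho) and the ANCOVA residual has σ²(1 − rho²). The ratio is (1 + rho)/2, which is below 1 for any rho below 1. Power at n = 24 with 0.6 as SD of change, so that the adjusted SD is 0.6 × √((1 + rho)/2):

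| rho | Variance ratio | Adjusted SD | Power, adjusted | Power, change score |
|---|---|---|---|---|
| 0.3 | 0.65 | 0.484 | 93.9% | 80.7% |
| 0.5 | 0.75 | 0.520 | 90.4% | 80.7% |
| 0.7 | 0.85 | 0.553 | 86.5% | 80.7% |
| 0.8 | 0.90 | 0.569 | 84.6% | 80.7% |

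With 0.6 as single-visit SD, adjusted against change-score power is 84.2% against 66.6% (rho 0.3), 90.4% against 80.7% (0.5) and 97.7% against 95.4% (0.7).

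**The case against.** The strongest reply is that the mismatch is real but need not cost power. Two of the three profiles above exceed 80%. The half-kept profile is the least favourable point between fully lost and fully kept, and at 28 per arm it reaches 79%. The article plans to carry forward the most recent assessment, so up to 28 per arm could be analysed, though carried-forward values may dilute the difference. The statistical section does not list the visits in the ANOVA either: with only two, the interaction is a 1-df change-score comparison with 80.7% power, matching the sample size if 0.6 is the SD of change. All of this stands, except that three visits is the natural reading of a design with three scheduled assessments.

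It is also true that baseline is not thrown away. As a level of time it makes the interaction a comparison of changes, which is valid in a randomised trial. Only the step from change score to covariate adjustment is lost.

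A reader might infer more than the documents support:

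- **That the trial is underpowered.** Power falls above or below 80% depending on the visit profile, the meaning of 0.6 and rho, none of which the article settles.
- **That the trial will yield no AT-BI estimate with a confidence interval.** The article does not exclude one, and follow-up contrasts and interval reporting are commonly left to an SAP.
- **That unequal visit spacing invalidates the ANOVA.** Sphericity concerns the variances of the paired differences between visits. Spacing alone does not show a violation, and corrections are likewise SAP matters.

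**Conclusion.** The concern holds in a limited form. The sample size is correct for a single two-group ACQ contrast, but the 80% attached to it does not describe the named test. At 24 per arm that test has 72% to 84% power over the profiles examined if 0.6 is the SD of change, and 57% to 97% if it is a single-visit SD with rho from 0.3 to 0.7. These ranges rest on compound symmetry, two-sided testing and the three-visit reading. They show that the power statement is not tied to the analysis; they do not show a shortfall.

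Two consequences do not depend on those assumed values. A significant three-visit interaction does not identify the better arm or the visit, and the article names no contrast that would. Baseline adjustment is more precise than a change-score comparison whenever rho is below 1 (step 4). The gain in variance is 10% to 35% for rho from 0.8 to 0.3; its size is assumed, its direction is not. This is a change that should be made: a better use of data already collected, not the repair of an invalid test.

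**What to change.** Before any results by group are seen, amend the plan to:

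- Name one primary contrast that matches the sample size: the AT minus BI difference in ACQ at one stated visit. End of intervention is the natural choice, but the choice is the investigators'.
- Estimate it with a 95% CI by ANCOVA, or by a mixed model with baseline ACQ as covariate and group-by-visit terms for the post-baseline visits.
- Take the follow-up contrast from the same model as the key secondary, so that persistence is addressed directly.
- Use the same approach for the continuous secondary outcomes, each with its own baseline value.
- Tie the 80% power statement to the named contrast, and say whether 0.6 is the SD of change or of a single-visit score.

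The cost is a documented amendment, since the ANOVA appears in the published article, plus a change of analysis model. No new data are needed. With 52 of 56 patients recruited by October 2025, the sample size is nearly fixed, and the analysis is the main place left to gain precision.

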### Analysis of the Population

The exclusion criteria will include participation in another study, current smokers or ex-smokers (who stopped smoking less than 1 year ago or had a smoking history of more than 15 pack-years), other associated lung or heart diseases, a diagnosis of cancer in the last 5 years, difficulty understanding any questionnaires, pregnancy, or psychiatric problems that prevent an understanding of the questionnaires. If a patient misses any session, the session will be rescheduled. Attending at least 75% of sessions will be considered the cutoff point to establish patient compliance for both groups [22-24]. An intention-to-treat analysis will be performed using the patient’s most recent assessment in case of withdrawal from the study or absence of data [25].

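### Intention-to-treat is limited to 15% missing data in one section and unlimited in another, and the limit sits at about the loss the trial plans for

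*Protocol article*

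**What the plan says.** Two sections of the protocol article set the rule for missing data.

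- **Statistical Analysis Planning:** "All the analyses will follow the intention-to-treat principles until 15% of the data are missing". The sentence covers every analysis, so it includes the primary comparison on the Asthma Control Questionnaire (ACQ).
- **Analysis of the Population:** "An intention-to-treat analysis will be performed using" the patient's "most recent assessment in case of withdrawal from the study or absence of data". No amount of missing data ends this commitment.

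The sample size paragraph in Statistical Analysis Planning uses the same percentage for expected attrition: "The required sample size will be 24 patients per group for a total of 48 patients", and then "a 15% loss will be considered, resulting in a total of 56 patients".

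The article does not say whether the 15% limit counts patients, visits or observations. It does not say whether the limit is judged per outcome, per arm or per time point, or what is done once it is passed.

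**The concern.** On its plain wording, the rule lets intention-to-treat lapse when missing data reach a level that becomes known only as the trial runs. More missing data calls for more care in keeping the randomised groups intact, so a rule that works the other way is hard to defend.

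Three things make it matter here.

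- The two sections give opposite instructions above 15%, and someone would have to choose between them once the amount of dropout is known.
- The limit is about the attrition the trial already expects, so reaching it is an ordinary outcome.
- The arms ask different things of patients: 16 supervised treadmill sessions against 8 individual counselling sessions with an activity monitor. Follow-up continues for 16 weeks after the intervention. Unequal dropout related to response is plausible, and an analysis restricted to patients with data would not be protected against it by randomisation.

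**Working it through.** **1. The plan's own figures.** The inputs are in Statistical Analysis Planning: difference 0.5 ACQ points, SD 0.6, power 80%, significance level 5% (two-sided assumed, since the article does not say).

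- Standardised difference: 0.5 / 0.6 = 0.833.
- A two-sample t test then needs 23.6, so 24 per group and 48 in total. Power at 24 per group is 0.807. The stated 24 and 48 reproduce.
- Allowance for loss: 48 × 1.15 = 55.2, so 56; or 48 / 0.85 = 56.5, so 57. The stated 56 follows from the first form and is one short of the second. This does not affect the present point.
- Going from 56 to 48 leaves room for 8 losses: 8 / 56 = 14.3%.

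**2. Where the limit falls.** Counting patients, 0.15 × 56 = 8.4. Eight losses (14.3%) stay below it and nine (9 / 56 = 16.1%) pass it.

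**3. Chance of passing it.** Assume that the 15% is a count of patients and that patients are lost independently with probability p. The chance is P(X ≥ 9) with X ~ Binomial(56, p).

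| True loss p | Basis | P(X ≥ 9) |
|---|---|---|
| 10% | assumption | 0.103 |
| 14.3% (8/56) | losses the sample size leaves room for | 0.407 |
| 15% | the plan's stated loss | 0.467 |
| 20% | assumption | 0.815 |

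At the attrition the trial expects, whether the limit is passed is not far from a coin toss.

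**4. The two rules side by side.**

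| Missing data | Analysis of the Population | Statistical Analysis Planning |
|---|---|---|
| Up to 15% | Intention-to-treat, last assessment used | Intention-to-treat |
| Above 15% | Intention-to-treat, last assessment used | Intention-to-treat ends; replacement not named |

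**5. What could follow, as an illustration only.** All of these inputs are assumptions: 28 patients per arm; 25% lost from aerobic training (7 patients) and 7% from behavioral intervention (2 patients), so 9 in total and just past the limit; those lost do not improve; the others improve by 0.6 points.

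- Mean improvement over all randomised patients: 0.75 × 0.6 = 0.45 with aerobic training and 0.93 × 0.6 = 0.56 with behavioral intervention. The difference is 0.6 × (0.25 − 0.07) = 0.108, or about 0.11.
- Mean improvement among patients with data: 0.6 in both arms, a difference of 0.

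For scale, 0.11 is about one fifth of the 0.5 points that the protocol calls clinically significant. It is also smaller than one standard error of the difference, 0.6 × √(2/28) = 0.16. The example shows a direction, towards no difference. It does not show a large distortion.

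**The case against.** The best defence is that the sentence is loosely worded and means less than it appears to. The Analysis of the Population section describes intention-to-treat together with use of the last assessment, so the 15% could be meant as a cap on that imputation. The figure is also fixed in advance and is triggered by the amount of missing data, not by the outcome results. What happens above the cap may be set out in a fuller protocol or analysis plan that is not shown.

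Part of this stands. The imputation-cap reading is possible, and an article need not describe every fallback. But that reading is not what is written, and it would still conflict with the other section, which uses the last assessment without limit.

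Some stronger readings are tempting, and the document does not support them.

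- **That the trial will switch to a completer or per-protocol analysis and give up the randomised comparison.** No replacement is named. An analysis of patients with data is the natural inference, not a stated plan. The attendance rule ("Attending at least 75% of sessions will be considered the cutoff point to establish patient compliance for both groups") is not tied to the 15% limit.
- **That the analysis population will be picked with the results in view.** The trigger is prespecified. What is open is its unit and its consequence.
- **That the limit and the planned loss are the same quantity.** One refers to data and the other to loss of patients, so the denominators may differ. The probabilities above hold only for a count of patients.
- **That the remedy is a new primary model.** The protocol plans a two-way repeated measures ANOVA with the last assessment carried forward, and this point gives no reason to replace it. A mixed model that assumes data missing at random would also show a difference of about 0 in the illustration if the patients left before the post-intervention assessment. Carrying the last value forward gives 0.11 there, but only because the example assumes that those who leave do not change.

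**Conclusion.** The point holds as a conflict between two sections and a badly fixed rule. Followed as written, the Statistical Analysis Planning sentence ends intention-to-treat for all analyses, including the primary one, at about the loss the trial plans for, while the Analysis of the Population section keeps it. With patients as the unit and independent losses, the chance of reaching that state is about 47% at a 15% loss and 41% at 8/56, ranging from 10% to 81% for true losses of 10% to 20%. Another unit, or losses that cluster, would change these figures but would not remove the conflict.

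The consequence is exposure to bias from differential dropout if the replacement is an analysis of patients with data. Its size cannot be derived from the document. The 0.11 above rests entirely on assumed inputs. The sample size is unaffected: 48 evaluable and 56 randomised.

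**What to change.** In Statistical Analysis Planning, delete the clause that ends intention-to-treat at 15%. State instead that all randomised patients are analysed in their allocated arm whatever the amount of missing data, in line with Analysis of the Population.

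If a 15% threshold is kept, define what it counts (patients or observations, for which outcome and at which visit). Let it trigger only additional missing-data sensitivity analyses, for example delta-adjusted imputation, and never a change of analysis population.

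The cost is one sentence and, if the threshold is kept, a little extra analysis work. The primary model and the sample size stay as they are. With 52 participants recruited by October 2025 and data collection still under way, the change should be made and dated before outcome data are examined by arm.
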